## End of trial (EoT)

Trial recruitment will cease in November 2019, regardless of the number of participants enrolled. EoT date, therefore, will be 12 weeks after enrolment of the 12^th^ trial patient or 12 weeks after the recruitment window closes, whichever happens first. At EoT, participants will return to clinical follow up within ASSESS-meso, which will continue until death, loss to follow up or withdrawal from the study. Data from ASSESS-meso will be used to evaluate overall survival at EoT.

|  |  | **Screening**  **Week 0*** | **Intervention**  **Day 0-14** | **3 days post-intervention**  **(Week 3)** | **Week 6** | **Week 12** |
| --- | --- | --- | --- | --- | --- | --- |
| **Clinical assessment** | Assessment of eligibility | X | **X** |  |  |  |
|  | History of pleural interventions | X |  | X | X | X |
|  | Previous oncological treatment | X |  |  |  |  |
|  | Medication history | X | **X** | X | X | X |
|  | WHO/ECOG performance status | X | **X** | X |  |  |
|  | Vital signs, pulse oximetry | X | **X** |  |  |  |
|  | Physical examination | X |  |  |  |  |
|  | Insertion of IPC (if not already in situ) | X |  |  |  |  |
|  | Pleural fluid drainage diary review | X |  | X | X | X |
|  | Documentation of AEs |  | **X** |  | X | X |
| **Blood tests** | Screening blood tests (HIV screen, hepatitis screen, immunoglobulins, random glucose, thyroid function tests) | X |  |  |  |  |
|  | Pregnancy test  (if female <55 yrs) | X |  |  |  |  |
|  | Coagulation panel | X |  |  |  |  |
|  | Trial blood tests (Full blood count, urea & electrolytes, liver function tests, C reactive protein) | X | **X** | X | X | X |
|  | Serum mesothelin | X |  | X | X | X |
|  | Pleural fluid sampling and storage | X | **X** | X | X | X |
|  | Mantoux test (if logistically possible, BCG arm only) | X |  |  |  | X |
| **Randomisation & intervention** | Random selection | X |  |  |  |  |
|  | Informed consent for TILT |  | **X** |  |  |  |
|  | Administration of OK432/BCG |  | **X** |  |  |  |
| **PROMS** | Breathlessness & chest pain VAS score | X |  | X | X | X |
|  | Daily VAS score completion |  |  |  |  |  |
|  | EQ-5D-5L QoL questionnaire | X |  | X | X | X |
| **Radiological imaging** | Chest x-ray | X | **X** | X | X | X |
|  | Thoracic ultrasound | X | **X** | X | X | X |
|  | CT chest (within preceding 2 weeks) | X |  |  |  | X |
| **Qualitative research** | Participant interviews |  |  |  |  | X |
|  | Focus groups with relatives/carers |  |  |  |  | X |

## Schedule of visits

* Screening visit is an ASSESS-meso –related activity, however it is included in the schedule of visits for clarity of the trial process

# QUALITATIVE RESEARCH

## Existing qualitative literature in MPM

MPM carries a significant physical, psychological and social burden, with specific issues arising as a result of the occupational nature of the disease.^85^ Physically many patients experience a rapid deterioration in physical health, which can be difficult for people who previously relied on their physical strength.^85^ Psychologically, some patients will have lived with anticipatory anxiety for years, and the diagnosis of mesothelioma is met with resignation and “stoical fatalism”.^86 87^ Depression is common, as is anger^88 89^. Patients may struggle with the burden of extensive medical interventions.^88 90^ Additionally the process of applying for compensation can be stressful, emotionally draining, and uncomfortable, particularly for those who consider themselves “self-reliant”.^88^

Although the experience of mesothelioma is well researched, it is not yet clear how patients view taking part in mesothelioma research. Considering the challenges of living with this condition, it would be understandable if people with mesothelioma were reluctant to participate in trials. Numerous studies acknowledge the difficulty of recruiting people with incurable or palliative conditions.^91-93^ However, evidence also suggests that many of these patients are interested in research, and may benefit from participation.^93^ Additionally, qualitative methods can be useful in clinical trial settings to help identify potential recruitment barriers and enhance participation.^94 95^

## Aim of qualitative research

The aim of the qualitative research is to explore the experiences of participants and their relatives/carers of taking part in TILT and to assess the acceptability of research processes to them. The qualitative research aims to answer the question “Was TILT acceptable to participants and their relatives?”

## Methodology for in-depth interviews

Following completion of the trial, a sample of participants will be invited to undertake an individual face-to-face interview with [name]. The sample will be purposively sampled to include participants from both arms of the study and participants who declined any element of the research, including those who declined to receive bacterial immunotherapy and those who requested not to be considered for future trials when they initially joined ASSESS-meso.

Interviews will be held after the final trial visit in order to prevent the interviews having any influence on trial outcomes.

At Week 6, participants will be provided with a patient information sheet describing the qualitative interviews. They will be given sufficient time to read it, and have the opportunity to discuss the research with a member of the trial team. To minimise inconvenience to participants, interviews will be conducted on hospital premises in a quiet and private room, however participants will be offered the option of being interviewed at home if they would prefer. Participants will be able to choose whether to have the interview on the same day as their final trial visit, or whether to schedule it for another day at their convenience. Interviews must be conducted within 14 days of the final trial visit.

Immediately before the interview, participants will discuss the qualitative study with the researcher, before being asked to provide written informed consent to participate. This will include specific consent to be audio-recorded, for the audio-recording to be stored electronically and for anonymised quotes to be used in the final report. Should a participant decline audio-recording this will not preclude their participation in interview, and the interviewer will seek their agreement to take notes instead.

Ideally, interviews will be held with just the participant and the interviewer present. However, the study also seeks to invite relatives and carers to take part, and this work will take place as focus group research as described in section 10.4. It is anticipated that patients will have different experiences and perspectives to their relatives/carers, and this is the reason for interviewing them separately. However, if a patient is reluctant to participate in the qualitative interviews unless their relative/carer is in attendance, then it will be permitted.

The interview topic guide will be reviewed and refined in collaboration with a group of patient and public representatives, who will also review the patient information leaflets. Patients will be asked about participating in TILT, including any problems they encountered, and any areas where the reality of trial participation differed from their expectations. Participants who received OK-423 will be asked about their experience. Participants who declined any part of TILT will be asked to discuss their reasons.

In addition, the following topics will be covered during the interviews:

- The TwiC design will be explained. Do participants find this methodology acceptable?
- Were the study follow up requirements manageable?
- What are their feelings about future trials and what factors might affect their participation?

Interviews will last approximately 1 hour. At the end of the interview, participants will be given the contact details of the local mesothelioma specialist nurse and the lead trial nurse in case any further support is required. We do not anticipate that the interviews will cause particular distress, but we are aware that talking about personal experiences can be upsetting. Therefore, the study processes for provision of support to a participant who becomes distressed will be used. For interviews, this comprises the interviewer asking the patient whether they would like to stop the interview at that point and acting according to their wishes. If the patient wishes to continue then the interviewer will do so but check again later in the interview. All participants who express distress during interview will be offered referral to an NHS clinical psychologist and all participants in the study as a whole will be provided with a list of useful further contacts for support. The interviewer ([name]) is an experienced clinician who has worked with this patient group for 8 years.

Interviews will be digitally audio-recorded, transcribed, anonymised and uploaded to QSR NVivo qualitative analysis software. Data will be analysed using thematic analysis, adopting an inductive, semantic and realist approach.^96^ Audio-recordings will be listened to and transcripts read twice for familiarisation, then inductively coded to develop an initial code list. A subset of interviews will be independently double-coded by an independent qualitative researcher and code-lists compared, refined and applied to the dataset, with further refinements as required. Coded segments of transcripts will be grouped into categories, and data explored to identify connections between categories and to develop a descriptive account of the dataset as a whole.

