## Consent

Participants who are randomly selected to receive either OK432 or BCG will be informed that they have been chosen to participate in a trial of a potential new treatment, and if they agree to participate they will definitely receive their allocated treatment. They will be provided with an information sheet about the trial, which will contain information about OK432 and BCG including potential risks and side effects. They will be allowed sufficient time, as determined by the patient, to consider trial entry, and will be offered the opportunity to discuss the trial with a member of the research team, and ask questions.

Once the participant is satisfied with the information they have been given they will be asked to provide written, informed consent to participate in TILT. A copy of the consent form will be sent to the coordinating trial centre (North Bristol NHS Trust) for documentation.

Patients who choose not to participate will be asked to provide brief reasons for non-participation, and will then return to follow up within ASSESS-meso. Their schedule of visits will be organised to match the TILT assessment schedule, in accordance with the flexible follow up stated in the ASSESS-meso protocol. These patients’ data will be collected as part of the feasibility outcomes for TILT.

Participants who are eligible for TILT but are allocated to the ‘control’ arm will continue follow up in ASSESS-meso, with a schedule of visits that matches the TILT assessment schedule. This is in accordance with the ASSESS-meso protocol, which includes the option for flexible follow-up visits, from weekly to 3 monthly. They will form a control group who will provide comparison data for the OK432 and BCG arms. If possible, **they will be blinded to the existence of the OK432 and BCG arms, and the TILT trial***.* This design replicates real-life clinical care where patients are informed about treatments as and when they are going to receive them, and not if they are not going to receive them.

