## Feasibility assessments

The primary outcome for the trial is feasibility. This will be based the following feasibility targets:

- Recruitment rates to time & target >66% at end of the trial
- Attrition rate of <20% (nb this relates solely to attrition due to loss to follow up or participant withdrawal, it does not include attrition due to participant death)
- Data completeness rates >90%

In addition, data will be collected on specific elements of the TwiC methodology to explore the acceptability of the trial design to participants. This will include determining how many participants in the control arm were aware that the intervention arm existed, and that they had been randomised to be controls. Information will also be collected on the number of participants who were randomly selected to receive either OK432 or BCG, but declined to do so. These participants will continue to be followed up in accordance with the TILT protocol. In order to determine whether participants who decline bacterial immunotherapy differ in any way to other study participants, their baseline characteristics and clinical outcomes will be compared with the control arm and with participants who received immunotherapy, as described in Section 13.

Data from ASSESS-meso will also be used to explore the characteristics and outcomes of patients who consented to join ASSESS-meso but declined to be considered for future trials.

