## Methodology for focus group sessions

Because previous qualitative research has highlighted the stoical nature of people with MPM,^85^ and because it is anticipated that relatives/carers are likely to have had different experiences of MPM and TILT, we will also undertake focus group sessions with participants’ relatives/carers. It is hoped that this will provide additional insight into the overall experience of MPM and participation in a research trial.

When trial participants are invited to join the qualitative interviews, they will also be asked whether they agree to their relative/carer being invited to a focus group session about the research. The participant information sheet for the qualitative research will include information on both the individual participant interviews and the focus group sessions for relatives/carers. If participants agree for their relatives to be approached, they will be asked to provide the name of their relative/carer, and that person will be invited to participate in a forthcoming focus group session. The invitation will be delivered either in person, if the relative/carer has attended the appointment with the participant, or via an invitation letter given to the participant to take home. Participants who do not wish a relative/carer to be invited to a focus group will still be eligible to participate in the one-to-one qualitative interviews.

Focus groups will be separated based on the arm of the trial the participant associated with the relative/carer was in. This is because the experience of relatives/carers will be different depending on which arm of the trial the participant was in. Separating the focus groups will also reduce the risk of distress or conflict arising as result of relatives/carers discovering that different participants were offered different options (see Section 14.4 for further details). Where the number of relatives/carers associated with a particular trial experience is small, e.g. the relatives/carers of participants who were offered bacterial immunotherapy but declined it, individual qualitative interviews will be offered.

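### The Week 6 qualitative information sheet has no exemption for controls, so it risks unblinding them before the Week 12 patient-reported outcomes and inflating the control-awareness count

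*Protocol*

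**What the plan says.** **Timing of the sheet.** Section 10.3 says: "At Week 6, participants will be provided with a patient information sheet describing the qualitative interviews". Recipients also "have the opportunity to discuss the research with a member of the trial team". No exception for controls is stated.

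**Who is in the qualitative work.** On interviews, section 10.3 says: "The sample will be purposively sampled to include participants from both arms of the study". On relatives, section 10.4 says: "Focus groups will be separated based on the arm of the trial the participant associated with the relative/carer was in". Section 10.4 adds that a single sheet covers both the interviews and the focus groups. Section 14.5 discusses relatives of participants in the observational arm.

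**Subject.** Section 10.2 gives the aim as to "explore the experiences of participants and their relatives/carers of taking part in TILT" and to assess whether the research processes were acceptable.

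**Blinding of controls.** Section 6.5 says of controls: "they will be blinded to the existence of the OK432 and BCG arms, and the TILT trial". That sentence opens with the qualifier that this applies if possible.

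**Protection of outcomes.** Section 10.3 says: "Interviews will be held after the final trial visit in order to prevent the interviews having any influence on trial outcomes".

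**Awareness measure.** Section 9.2 plans "determining how many participants in the control arm were aware that the intervention arm existed, and that they had been randomised to be controls". The count also appears in section 2.3 and in the list under the primary outcome in section 13.1. No section says when it is taken, and the schedule of visits has no row for it.

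**The concern.** The protocol delays the interview to protect outcomes but issues the document that describes the interview, with an offer to discuss it, six weeks before the last outcome visit. For participants offered OK432 or BCG this does no harm, because they already know about TILT. Controls have signed no TILT consent and are meant not to know that the trial exists.

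Two things are at stake. First, the protocol's account of the TwiC design argues that disappointment in a standard-care arm could affect patient-reported outcomes, and that not informing controls removes this problem. A control told at Week 6 answers the Week 12 questionnaires without that protection. Second, the number of aware controls is meant to show whether the design keeps controls uninformed in practice. If the sheet makes them aware and the question comes later, the count mixes accidental leakage with disclosure that the protocol scheduled.

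**Working it through.** The plan gives no figure to reproduce. The check sets the sections side by side and adds simple counts.

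**1. Are controls among the recipients?** The Week 6 sentence says only participants, and the sampling sentence refers to both arms in a three-arm trial. Two narrower readings are possible: that both arms means the two active arms, or that participants means only those who signed TILT consent (sections 5.5 and 6.5). Section 14.5 rules these out for the qualitative work as a whole. It plans separate focus groups partly because relatives of people not offered immunotherapy may react differently. Under section 10.4, relatives are reached through the participant, and one sheet covers interviews and focus groups. Controls whose relatives are to be approached must therefore be among the recipients.

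**2. Would sampling spare the controls?** Section 10.6 plans 20 interview invitations and section 6.6 plans 12 randomised participants. Since 20 > 12, selection within the trial would not by itself leave out any of the 4 controls.

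**3. What is measured after the sheet?** Section 9.1 sets visits at Weeks 3, 6 and 12, and the schedule lists VAS and EQ-5D-5L at each.
- Follow-up remaining after Week 6: (12 − 6) / 12 = 50%.
- Scheduled post-baseline assessments clearly after the sheet: 1 of 3 (Week 12). The order of events within the Week 6 visit is not given, so I do not count Week 6.
- Section 9.3 also plans daily completion for a period between Weeks 0 and 3. Most patient-reported data therefore precede the sheet, but the Week 12 value does not.

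**4. How far can the awareness count move?** Section 6.6 gives 4 controls, so one control is 1/4 = 25 percentage points. The effect of the sheet ranges from 0 of 4 (neutral wording, or awareness recorded before Week 6) to 4 of 4 (revealing wording and awareness recorded afterwards). The plain English summary still gives 24 people with 16 selected, which would leave 8 controls and 1/8 = 12.5 points each. I use 4 because sections 6.4 and 6.6 and the flowchart agree on 12 in total.

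**5. Is there time to move the sheet?** Section 10.3 allows interviews up to 14 days after the final visit. At present the time to consider runs from Week 6 to two weeks after Week 12, about 6 + 2 = 8 weeks. Moving the sheet for controls to the end of Week 12 leaves up to 2 weeks. Section 14.7 accepts about 24 hours as the usual thinking time for consent to the trial treatment itself.

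**The case against.** The strongest reply is that disclosure at Week 6 is inferred. The sheet is said only to describe the interviews. Section 10.3 lists explanation of the TwiC design as an interview topic, so it comes after the final visit. Controls are consented ASSESS-meso participants, and a sheet could be framed around that study without naming TILT, OK432 or BCG. The protocol speaks of information sheets in the plural, so a control version is not excluded. This stands as far as certainty goes. It does not supply a safeguard: no neutral or control-specific sheet is described, and interviews about taking part in TILT are hard to describe without revealing TILT.

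Other points also stand. Blinding applies only if possible, although that hardly covers a scheduled and avoidable disclosure. The question about inviting a relative is tied to the interview invitation, which section 10.3 elsewhere places after trial completion, so a reader should not infer that relatives are necessarily raised at Week 6. The sample also includes people who declined consideration for future trials. They have no TILT Week 6, so the sentence is loosely drafted.

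On importance, patient-reported outcomes are exploratory secondary measures in a very small trial whose treated participants are unblinded anyway. Awareness is listed under the primary feasibility outcome but has no pass or fail threshold.

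**Conclusion.** The point holds as a risk. Section 10.3 sets a time for the sheet that conflicts with the intended blinding of controls and with the section's own reason for delaying interviews, and nothing in the protocol prevents the consequence. Up to 4 of 4 controls could be unblinded before the Week 12 VAS and EQ-5D-5L, and each would move the awareness proportion by 25 percentage points if awareness is recorded after the sheet. This rests on two assumptions the protocol leaves open: that the sheet reveals TILT, which is likely given its subject, and, for the awareness count only, that awareness is recorded after Week 6.

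A reader might go further and infer that controls will be told of TILT at Week 6, that the awareness count will reach 4 of 4, or that the feasibility decision would change. The document does not support these. The sheet's wording is not shown, the time of the awareness record is not fixed, and the feasibility thresholds cover recruitment, attrition and data completeness only. The correction is still worth making before any control reaches Week 6, because a control who has been told cannot be blinded again.

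**What to change.** In section 10.3, and for the relative invitation in section 10.4, state that controls and their relatives receive the sheet only at the end of the control's Week 12 visit. Fix the order at that visit:

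1. Week 12 patient-reported outcomes are completed.
2. Control awareness is recorded with a question that does not itself reveal the intervention arms, for example an open question about other studies or treatments the person has heard of.
3. The sheet is handed over and discussion offered.

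Add the awareness item to the Week 12 column of the schedule for controls, and name that record as the source for the measure in sections 2.3, 9.2 and 13.1. A control who does not reach Week 12 would have no record, so the count should be reported over those assessed. Participants offered OK432 or BCG, including those who declined, already know of TILT and keep Week 6.

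The cost is protocol wording and one eCRF item. Controls would have at most 14 days to consider the interview. A same-day interview, which section 10.3 offers for convenience, would become less practical for them. A neutral control sheet at Week 6 would avoid both drawbacks but is weaker protection, because it depends on the wording and on what is said in the accompanying discussion.
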